## 3 Methods

### 3.1 Study design

This study employs a randomized community trial design to assess the impact of a novel Food Forest reforestation technique that emphasizes the use of endemic and food-producing species. The goal is to enhance food sovereignty among coastal families in the Santa Elena Province, Ecuador. This initiative, a collaborative effort by Nedetel and CECAPROF Corporación Ecuatoriana De Capacitación (two companies that serve the area), aims to address the dual challenges of malnutrition and low average family incomes in the region (33). Participants for the study will be recruited from rural areas within the Colonche Parish of the Santa Elena Canton, a geographical area detailed in Figure 1 (34, 35). The study randomly allocated one commune to receive the Food Forest intervention, while a similarly characterized commune was randomly assigned as a control group, receiving no intervention. This randomization process ensures that the study meets the criteria of a randomized community trial. In consideration of ethical concerns, we have planned a delayed intervention for the control group. After the study period, the control commune will also receive the food forest intervention, contingent on securing additional funding. This phased approach allows for a scientifically rigorous assessment of the intervention's effects while ensuring that both communities ultimately benefit from the food forest initiative. The intervention strategy was developed based on insights from prior research, supplemented by consultations and interviews with experts in nutrition and reforestation, ensuring that the Food Forest initiative is ecologically viable and tailored to meet the nutritional and economic needs of the local communities involved.

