### 3.3 Sampling

In our study within Colonche Parish, we will engage in a randomized selection process to choose one commune for the treatment group, where the Nutritional Forest will be implemented, and two communes for the control group, which will not have access to the Nutritional Forest. This selection process will encompass all communes of the Parish, including Aguadita, Ayangue, Bajadita de Colonche, Bambil Collao, Bambil Desecho, Calicanto, Cerezal Bellavista, Febres Cordero, Jambelí, Las Balsas, Loma Alta, Manantial de Guangala, Manantial de Colonche, Monteverde, Palmar, Río Seco, Salanguillo, and San Marcos. Each commune will be treated as an individual cluster, and a random cluster sampling method will be employed to ensure a fair and unbiased selection of the communes for both the treatment and control groups.

The random selection will be carried out using a lottery system where each commune will be assigned a unique identifier, and a computerized random number generator will select the treatment commune and control communes. This approach minimizes selection bias and ensures a randomized, equitable process.

The 1:2 allocation ratio (one treatment commune and two control communes) was chosen due to feasibility considerations and community input. The local community expressed a preference for starting the Nutritional Forest intervention in one commune initially, allowing for more focused implementation and monitoring. This also aligns with the available resources and ensures that the intervention can be tailored to the specific needs of the treatment community.

Following the selection of the commune, we will proceed to sample households within each of the chosen commune. Household selection will be conducted using a two-stage sampling method. First, a list of households within each commune will be obtained from local community records. Second, a systematic sampling method will be applied to randomly select households from this list, ensuring that the sample is representative of the entire community. This step will ensure that our assessment captures a broad spectrum of community experiences and perspectives regarding the impact of the Nutritional Forest intervention.

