### 3.11 Ethics and dissemination

The Kennedy Clinic's Institutional Review Board (IRB) in Guayaquil has granted approval for this study, under the code HCK-CEISH-2022-006. At every phase of the research, informed consent will be rigorously obtained and mandated, adhering to the ethical standards for research involving human participants. To ethically support the control group during the study, we will provide alternative community support measures, such as nutritional education and health assessments, to ensure both communities receive beneficial resources. Additionally, we have planned a delayed food forest intervention for the control group as soon as funding allows, ensuring that both communities ultimately benefit from the initiative. This approach has been designed in collaboration with community leaders to align with ethical standards and community expectations.

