### 4.2 Content of intervention

The community's role in establishing and maintaining the food forest is structured through active participation in key phases of the project. Community members are involved from the onset in activities such as site preparation, planting, and periodic maintenance. Harvests are organized so that community members can collectively decide on usage, ensuring fair distribution and communal benefit. Regular meetings will also allow the community to provide input on project development, further strengthening local engagement and commitment to long-term maintenance.

The intervention comprises two key activities (plantations and reforestation workshops), conceived and implemented by Nedetel and CECAPROF, within the territories of the Colonche Parish communes. Designed to run concurrently, these activities span in total 5 years, allowing for a synchronized approach. This strategic implementation aims to address malnutrition and enhance the average family income in Santa Elena Province, contributing to overall community wellbeing.

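### Section 3.3 assigns the arms before households are sampled, asked for consent and measured at baseline, so who joins and how they answer can differ by arm

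*Protocol article*

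**What the plan says.** Section 3.3 uses a single draw to pick the communes and give them their arms: "a computerized random number generator will select the treatment commune and control communes". Household work comes next: "Following the selection of the commune, we will proceed to sample households within each of the chosen commune". Within each commune a household list is obtained, and "a systematic sampling method will be applied to randomly select households from this list".

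Section 3.1 puts allocation in the past, "The study randomly allocated one commune to receive the Food Forest intervention", and recruitment in the future, "Participants for the study will be recruited from rural areas within the Colonche Parish of the Santa Elena Canton". Section 3.3 describes the same draw in the future tense, so the article leaves open whether it has been made. On either reading, assignment precedes household sampling.

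On consent, section 3.11 says: "At every phase of the research, informed consent will be rigorously obtained and mandated". It does not place consent before the lottery or before its result is disclosed. Section 3.7 hides participants' identities from researchers and statisticians, which is not masking to arm. Section 4.2 makes the intervention visible: "Community members are involved from the onset in activities such as site preparation, planting, and periodic maintenance".

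**The concern.** Randomising communes protects the comparison only if households enter each arm in the same way. Here recruitment follows assignment, and this opens two routes to bias.

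- **Consent.** The arms offer different things. Section 3.2 speaks of direct food access for participating families. Section 3.11 offers the control side nutritional education, health assessments and a later forest if funding allows. Households may accept or refuse for reasons that differ by arm.
- **Baseline answers.** HFIAS, SF-36, WHOQOL-100, PedsQL and the dietary questionnaires are reported by participants or caregivers. A household that knows its commune will or will not receive the forest may describe its needs differently.

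The second route matters more for the planned longitudinal analysis. Need over-reported at baseline in one arm looks like improvement if later answers revert.

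**Working it through.** **1. Order of steps**

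| Step | Where | Position |
|---|---|---|
| Communes and arms drawn together | 3.3 (3.1 in the past tense) | first |
| Household list and systematic sample | 3.3 | after the draw |
| Consent of sampled households | 3.11 | no step places it earlier |
| Baseline on sampled households | 3.8 | after sampling |
| Concealment of result, or masked interviewers | nowhere in the article | none |

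That consent and baseline follow assignment comes from the stated sequence. That the arm is known at that point is an inference from the open intervention, the involvement of community leaders (3.11) and the absence of any concealment step.

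**2. The plan's own household number (3.4)**

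n0 = 1.96² × 0.5 × 0.5 / 0.05² = 384.2 (stated: about 384). With 968 households, 384.2 / (1 + 383.2/968) = 275.2 (stated: 276). The plan raises this to 300 per commune, and 276/300 = 0.92 implies 8% attrition. The figures reproduce. The comparison is 300 v 300 with one control commune (abstract, 3.1) or 300 v 600 with two (3.3).

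**3. What analysis of change can and cannot remove**

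The between-arm difference in change is the follow-up difference minus the baseline difference. Take no true effect.

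- Stable selection difference s at both visits: s − s = 0. It cancels.
- Reporting shift r at baseline only: 0 − r = −r. It passes through in full.
- Selection on future trend, where joiners in one arm would have changed by t more anyway: t. It stays.
- Single-visit comparison without baseline adjustment: s. It stays.

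**4. Illustrative size of s in an unadjusted single-visit comparison**

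The documents give no acceptance rates, so all inputs except the household numbers are assumptions.

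The mean among joiners differs from the full-sample mean by refusal rate × joiner-refuser gap. With acceptance of 95% v 75%, the difference in refusal is 0.20. A gap of 0.3 to 0.5 SD gives 0.20 × 0.3 = 0.06 to 0.20 × 0.5 = 0.10 SD.

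- 300 v 300: SE = √(1/300 + 1/300) = 0.0816 SD; bias/SE = 0.7 to 1.2.
- 300 v 600: SE = √(1/300 + 1/600) = 0.0707 SD; bias/SE = 0.8 to 1.4.

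P(|Z + bias/SE| > 1.96) is 11% to 23% for 300 v 300 and 14% to 29% for 300 v 600.

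A second illustration uses binary food insecurity, truly 50% in both arms, with joining related to insecurity only in the forest commune:

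| Insecure v secure joining | Observed insecurity | Rejects, 300 v 300 | Rejects, 300 v 600 |
|---|---|---|---|
| 85% v 80% | 51.5% | 7% | 7% |
| 90% v 80% | 52.9% | 11% | 13% |
| 90% v 70% | 56.3% | 34% | 43% |

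All these rates ignore clustering by commune.

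**The case against.** The strongest reply is that the article states the order of the draw and the sampling, but not when the result is announced or what households and interviewers are told. Consent scripts and announcement timing are often left to a full protocol. This stands as a limit: knowledge of arm is probable, not documented. It does not remove the point, because the article itself puts assignment before sampling.

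Four stronger readings are tempting, and the documents do not support them.

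- **That baseline adjustment cannot help.** Section 3.10 names comparisons of change and mixed-effects models over repeated measures. These would largely cancel a stable difference in level.
- **That 3.3 claims the whole process is free of selection bias.** The sentence "This approach minimizes selection bias and ensures a randomized, equitable process" directly follows the description of the commune lottery and refers to it. Household sampling is described later and separately.
- **That control households have no reason to join.** Section 3.11 offers them education, health assessments and a delayed forest, and section 4.3 offers participants incentives. Section 4.1 says the forest's benefits are shared among all community members, so access may not depend on joining the survey, although 3.2 points the other way. The documents fix neither the direction nor the size of a consent gap.
- **That the primary outcome is wholly self-reported.** Section 3.9.1 describes a questionnaire, but 3.5.1 and 3.10 assign anthropometry to everyone except older adults. Weight and height are much less open to reporting by arm, though still open to differential consent.

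**Conclusion.** The point holds as a preventable risk created by the stated sequence. Consent and self-reported baseline can differ by arm; nothing shows that they will. The exposed parts are arm-dependent reporting at baseline, selection on future trend, and those chi-square, t-test or rank comparisons in 3.10 that are made on single-visit levels without baseline adjustment.

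No size can be derived from the documents. The 0.06 to 0.10 SD, and the rejection rates that go with it, depend on assumed acceptance rates and an assumed joiner-refuser gap, and apply to an unadjusted comparison. A reader might take 11% to 29% as the trial's true false-positive rate. That would be wrong: with one treated commune and clustering ignored, the nominal 5% is not the real starting point either.

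The sequence should be changed before fieldwork, because a baseline taken under known allocation cannot be repaired afterwards.

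**What to change.** Rewrite the sequence in 3.3:

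1. Draw the study communes from the 18 without assigning arms.
2. In all of them, list households, take the systematic sample, obtain consent and complete baseline, using one script.
3. Only then draw, or at least announce, which commune receives the forest, before site preparation starts.

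Drawing in two steps does not change any commune's chance of treatment. With three study communes it is 3/18 × 1/3 = 1/18, as in a single draw.

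If the draw has already been made, as the tense in 3.1 suggests, finish consent and baseline in every commune before the result is announced, where that is still possible. In either case, report households approached, refused and consented by commune.

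The households, staff and visits stay the same. The cost is delay: site preparation and commune-specific planning with community leaders must wait until baseline fieldwork is complete everywhere, and this has to be squared with the early community involvement described in 3.11 and 4.2. The change does not address the separate problem of having only one treated commune.

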### 3.4 Sample size

A total of 968 families were considered as the research units in this study. Therefore, considering a margin of error of 5% and a confidence level of 95%, the estimated sample size before considering the finite population correction was approximately 384, according to Equation 1 where n is the sample size, Z is the Z-score associated (1.96) with the desired confidence level (95%), p is the estimated proportion of the attribute present in the population (0.5), and E is the margin of error (5%). After applying finite population correction, the estimated sample size was reduced to 276. This adjustment is made because the population is relatively small, and the correction helps avoid overestimating the required sample size. The sample of families in each commune is 300 because attrition is expected. The heads of the household will be surveyed regarding the nutritional, socioeconomic, and health situation of the family. The primary sampling unit for this study is the household (family unit), with a total sample size of 300 families. Within each family, specific questionnaires will be administered based on the nature of the assessment. The *Household Food Insecurity Access Scale (HFIAS)* will be completed by the head of the household to capture food security at the family level. For health and quality of life assessments, individual adult members will complete the *Short Form-36 Health Survey (SF-36)* and the *World Health Organization Quality of Life (WHOQOL-100)* questionnaire to evaluate personal health and quality of life outcomes. Additionally, the *Pediatric Quality of Life Inventory (PedsQL)* will be administered to caregivers of children to assess child health-related quality of life. This approach ensures comprehensive measurement across family and individual levels, providing both household-level insights and individual health metrics.

Formula for sample size estimation.

(1)
$$\begin{array}{l} n=\frac{Z^{2}\times p\times \left(1-p\right)}{E^{2}} \end{array}$$

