Building on this foundation, Food Forests offer a promising intervention by combining ecological sustainability with agricultural productivity. These diverse, multi-layered systems go beyond traditional forestry, providing food, livelihood opportunities, and environmental benefits (25–29). Evidence from a case study in Sangthong district, Laos, illustrates the potential of Food Forests, where even less affluent families significantly improved their dietary quality through integrated agroforestry systems (30). Despite these promising indicators, however, there is a notable gap in the literature, as few comprehensive studies have rigorously quantified the impact of Food Forest interventions on nutritional, economic, and health outcomes, with most existing research being qualitative or retrospective in nature (31, 32).

The present study aims to address this gap by evaluating the impact of a Food Forest initiative on the nutritional status, socioeconomic conditions, and health outcomes of rural communities in the Colonche Parish of Santa Elena Province, Ecuador. Using a randomized, controlled trial design, this research will provide empirical evidence on the effectiveness of Food Forests as a solution to malnutrition and poverty. The findings from this study have the potential to inform similar initiatives in rural settings across Latin America and other LMICs, fostering socioeconomic development and environmental sustainability.

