### 4.3 Potential pitfalls and unintended effects

Several potential pitfalls and unintended effects could arise during the implementation and evaluation of the Food Forest initiative. One key challenge is the variability in participant engagement. Some community members may be more actively involved in the initiative (e.g., planting, maintaining, or harvesting), while others may not fully engage, leading to differences in outcomes that may not directly reflect the intervention's effectiveness. Additionally, external factors, such as adverse weather conditions, could impact the growth of the Food Forest and, consequently, its effects on nutritional outcomes. Furthermore, there may be difficulties in retaining participants for follow-up assessments over the twelve-month study period, particularly given the rural nature of the setting, which may affect the continuity of data collection. To mitigate these risks, we will implement regular check-ins with participants, provide incentives to encourage continued engagement, and monitor environmental conditions closely to assess their impact on the project. By anticipating these challenges, we aim to minimize their potential effects on the study's results.

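### Section 3.4 sizes a one-commune prevalence survey, so its 5% margin does not describe the intervention-control comparison

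*Protocol article*

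**What the plan says.** Section 3.4 (Sample size) sets out the whole calculation. Its population is one commune: "A total of 968 families were considered as the research units in this study", and section 3.2 gives 968 as the number of households in each commune. Equation 1 is n = Z²p(1−p)/E², with Z = 1.96, p = 0.5 and E = 5%. From it, "considering a margin of error of 5% and a confidence level of 95%, the estimated sample size before considering the finite population correction" is given as about 384, and then: "After applying finite population correction, the estimated sample size was reduced to 276". The last step is "The sample of families in each commune is 300 because attrition is expected". No attrition rate is given. Later, the same section gives 300 families as the total sample size.

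The comparison to be made is described elsewhere. Section 3.3 randomises communes as clusters, one to treatment and two to control; the Abstract and section 3.1 have one control commune. Section 3.10 compares the intervention and control groups with two-sided tests at p < 0.05, on binary outcomes such as food security and continuous ones such as BMI, income and dietary diversity. It adds mixed models for the repeated measurements. Nutritional status, the primary outcome domain in 3.9.1, is to be analysed per individual.

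**The concern.** Equation 1 answers the question of how closely a survey can estimate one prevalence in one enumerated commune. It has no second group, no difference to detect and no allowance for the commune as the unit of randomisation. The finite population correction fits the description of a fixed list of 968 families. It does not fit an intervention effect meant to carry further, and the Introduction says "The findings from this study have the potential to inform similar initiatives in rural settings across Latin America and other LMICs".

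The 5% is the only precision figure in the article. If it is carried over to the arm comparison, a null result could be read as excluding effects that the trial had little chance of detecting. The attrition allowance has the same weakness, because it is attached to the single-commune margin. Section 4.3 also warns that "there may be difficulties in retaining participants for follow-up assessments".

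**Working it through.** **Inputs from the article.** Z = 1.96, p = 0.5, E = 0.05, N = 968, 276 and 300 families (3.4); 968 households per commune (3.2); one control commune (Abstract, 3.1) or two (3.3). **Assumed here:** p = 0.5 in both arms, communes of equal size, and illustrative ICCs and attrition, since the article gives neither.

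**1. Reproduce the stated figure.** n₀ = 1.96² × 0.25 / 0.05² = 384.16. With the correction, 384.16 / (1 + 383.16/968) = 275.2, rounded up to 276. The figure reproduces. The implied attrition allowance is 1 − 276/300 = 8%.

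**2. Where 5% holds.** One commune, one proportion, 276 families:
- without the correction, 1.96 × √(0.25/276) = 5.9 points;
- with it, 5.9 × √((968 − 276)/967) = 4.99 points.

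With 300 families and no correction, 1.96 × √(0.25/300) = 5.7 points before any attrition.

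**3. The arm difference, before clustering.** Half-width = 1.96 × √(0.25 × (1/n₁ + 1/n₂)). For 276 vs 276 this is 8.3 points. The corrected column applies √((968 − n)/967) to each commune's term, where n is the number sampled in that commune.

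| Families (intervention vs control) | Without correction | With correction |
|---|---|---|
| 276 vs 276 | 8.3 | 7.1 |
| 276 vs 552 | 7.2 | 6.1 |
| 300 vs 300 | 8.0 | 6.7 |
| 300 vs 600 | 6.9 | 5.8 |
| 150 vs 150 (300 in total) | 11.3 | 10.4 |
| 100 vs 200 (300 in total) | 12.0 | 11.4 |

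The smallest value is 5.8. At 276 per commune without the correction, the difference detectable with 80% power is about 2.80 × SE: 2.80 × 8.34/1.96 = 11.9 points (1 vs 1 commune) or 2.80 × 7.22/1.96 = 10.3 (1 vs 2). Power for a true 50% vs 55% is 22% or 27%.

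**4. Commune clustering.** Design effect = 1 + (276 − 1) × ICC; the half-width is multiplied by its square root.

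| Assumed ICC | Design effect | 1 vs 1 | 1 vs 2 |
|---|---|---|---|
| 0.001 | 1.275 | 9.4 | 8.2 |
| 0.01 | 3.75 | 16.2 | 14.0 |
| 0.05 | 14.75 | 32.0 | 27.7 |

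More families per commune cannot remove this component. As their number grows, the 1 vs 1 half-width tends to 1.96 × √(2 × 0.25 × ICC), which is 13.9 points at ICC 0.01.

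**5. Attrition, illustrated at an assumed 20%.** 300 × 0.8 = 240 families per commune. The single-commune margin with the correction is 1.96 × √(0.25/240) × √(728/967) = 5.5 points. The uncorrected difference, before clustering, is 1.96 × √(0.25 × 2/240) = 8.9 points (1 vs 1) or 1.96 × √(0.25 × 1.5/240) = 7.7 (1 vs 2).

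**The case against.** The strongest reply is that section 3.4 does what it says. It ties E to the proportion of an attribute in a population, and nowhere does the article call 5% the precision of the treatment effect. That is correct: a reader might infer such a claim, but the text does not make it. What stands is that 3.4 is the only stated basis for the sample of a comparative trial, and it leaves that inference open.

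The finite population correction can be defended in part. Section 2.1 presents Colonche as a case study, 3.2 focuses on the residents of one commune, and the Introduction claims only a potential to inform others. The conclusion does not need the correction to be wrong, because the arm-difference margin stays above 5 points when it is kept.

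The half-widths above are for a family-level proportion at one time point, at the worst-case p. They match a planned comparison such as household food security, but they are not the precision of the primary outcome. That outcome is individual-level and partly continuous, with about 3,875/968 = 4 people per household, and section 3.10 plans models that use the repeated measurements. This limits what the figures can be used for. It does not rescue Equation 1, which does not address that outcome either.

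A reader might also infer that true precision is several times worse than 5%. That depends wholly on the ICC: at 0.001 the half-width is less than twice 5 points, at 0.05 more than six times with one control commune. The article states no ICC, so no single multiple is supported.

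On attrition, 4.3 plans check-ins and incentives, and the 20% used above is an assumption that moves the single-commune margin by only half a point.

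Finally, a full protocol or SAP may contain a power calculation. The point does not rest on its absence: the article prints a formula with all its inputs, and that formula is for a different question.

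**Conclusion.** The point holds, as a wrong basis for the sample size. It is not an arithmetic error: 384 and 276 both reproduce. The 5% margin is met at 276 families only for one proportion, in one commune, with the finite population correction. For the arm difference in a family-level proportion at p = 0.5, before clustering, the half-width is 5.8 to 8.3 points over 276 or 300 families per commune, one or two control communes, and correction kept or dropped. Without the correction it is 11.3 to 12.0 if 300 is the overall total. Clustering adds to this by an amount the article gives no means of fixing.

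Two further inferences are not supported. The 8% allowance does not show that 300 families tolerate 8% loss in general, because it exists only with the correction. Nor do the results show that more families are needed, since more families would not remove the between-commune component. Severity: should-fix.

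**What to change.** Rewrite section 3.4 without enrolling more families.

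- Say that the 5% margin describes a prevalence estimate in a single commune, with the finite population correction, and nothing else.
- Reconcile 300 families per commune with 300 as the total, and one control commune (Abstract, 3.1) with two (3.3).
- State the confidence-interval half-width or detectable difference for the between-arm contrast, without the finite population correction, over a range of ICCs labelled as assumptions. With one commune against one, the trial cannot estimate the between-commune variance itself, so the range must come from outside it.
- Give the same for the primary outcome on its own scale, continuous or individual-level, rather than only as a proportion.
- Show that precision at several assumed attrition levels. Note that the 8% allowance applies only to the corrected single-commune margin, and that without the correction 300 families give ±5.7 points in one commune before any loss.
- Reconcile the 12-month follow-up (Abstract, 3.10, 4.3) with assessments at 1, 3 and 5 years (3.8), so that the attrition range matches the schedule.

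The cost is a rewritten section and a less favourable stated precision. Recruitment does not change.
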